## **5.0 STUDY TREATMENT**

### **5.1 Regimens, Administration, and Duration**

Study treatment is open label telmisartan.

All subjects will receive telmisartan 40 mg po daily for the 24 week study duration.

For the purposes of managing hypotension or maintaining stable renal function, if a subject's sbp becomes <100mmHg or serum creatinine significantly increases (in the eyes of the investigator) while on telmisartan therapy, a dose reduction to 20mg po daily will be allowed.

### **5.2 Study Product Formulation and Preparation**

Telmisartan 40mg tablets must be dispensed in the original bottle with the desiccant provided. Store at room temperature (25°C, 77°F) and protect from moisture.

### **5.3 Pharmacy: Product Acquisition, Distribution, and Accountability**

#### Study Product Acquisition/Distribution

Telmisartan will be purchased for the study following IRB approval. The use of telmisartan in this setting qualifies for an IND waiver, which will be obtained in a timely fashion.

Telmisartan will be provided at no cost to the subject. However, subjects will remain responsible for providing all other needed medications (including but not limited to ART).

### **5.4 Concomitant Medications**

#### Prohibited Medications

The prohibited medications with telmisartan are listed in Section 4.2.3.

## 6.0 CLINICAL EVALUATIONS

### 6.1 Schedule of Events

|                                                                                 | Screen | Baseline* | Week 1 | Week 2 | Week 6 | Week 12* | Week 18 | Week 24* |
|---------------------------------------------------------------------------------|--------|-----------|--------|--------|--------|----------|---------|----------|
| Informed Consent, Patient's Bill of Rights, HIPPA, medical information release  | X      |           |        |        |        |          |         |          |
| Targeted physical exam with weight, blood pressure                              |        | X         | X      | X      | X      | X        | X       | X        |
| Complete physical exam and height                                               | X      |           |        |        |        |          |         |          |
| CT- L4/5                                                                        |        | X         |        |        |        |          |         | X        |
| Mid-waist, hip and neck circumferences and waist/hip ratio                      | X      | X         |        |        |        |          |         | X        |
| HIV-1 RNA                                                                       | X      | X         |        |        |        |          |         | X        |
| Safety labs**                                                                   | X      | X         |        |        | X      | X        | X       | X        |
| CD4 cell counts                                                                 |        | X         |        |        |        |          |         | X        |
| Fasting lipids, hsCRP, banked serum and plasma                                  |        | X         |        |        |        | X        |         | X        |
| Urine samples for markers of oxidant stress and endothelial activation, protein |        | X         |        |        |        | X        |         | X        |

\* Entry, week 12, and week 24 laboratory evaluations are required to be fasting (at least 8 hours).

\*\*Safety labs include: CBC with differential, chemistry panel [including liver enzymes (ALT, AST, Alk Phos) and total bilirubin, serum creatinine], urine or serum pregnancy test. All safety labs, HIV-1 RNA, and CD4 cell counts will be done at local certified laboratories.

## **6.2 Timing of Study Evaluations**

### **Visit I Screening**

After obtaining informed consent, study participants will undergo a series of screening evaluations to determine eligibility. The waist and hip measurements will be performed first to determine if the subject meets criteria (defined for women/men as: waist circumference > 94/95 cm or a waist-to-hip ratio > 0.88/0.94). All sites will be trained in the procedures for obtaining waist and hip measurements, and these will be collected in triplicate.

If eligible, the subject will undergo a single 5 mm slice CT scan at the level of L4-L5, and the image will be sent to the central reading center in electronic format. The CT scan will not be scheduled until eligibility is confirmed by exam and laboratory parameters.

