### **4.2 Exclusion Criteria**

- 4.2.1 Pregnancy (current or within the past 6 months) or nursing.

Note: For females of reproductive potential [defined as women who have had menses in the 12 months prior to entry, or who have not undergone surgical sterilization (hysterectomy, bilateral oophorectomy, and/or tubal ligation)], will need a negative serum or urine pregnancy test in the 48 hours prior to entry. If participating in sexual activity that could lead to pregnancy, study participants must use contraception while on study drug and for 4 weeks after going off study drug.

- 4.2.2 Uncontrolled hypertension. If subjects are currently on a stable anti-hypertensive regimen, they must be willing to add telmisartan to their current regimen and provide documentation from their cardiologist or prescribing physician that the addition of telmisartan is acceptable/not contraindicated. To minimize the potential for aggravation of renal function, if subjects require titration of their antihypertensive regimen while on study, it is asked that ACE inhibitors not be titrated unless other options are not available.

4.2.3 Prohibited concomitant medications: Thiazolidinediones, other members of the angiotensin receptor-blocking class (losartan, irbesartan, olmesartan, valsartan, candesartan), nelfinavir, etravirine. Subjects taking nelfinavir or etravirine will be excluded due to the possibility of increased drug levels via inhibition of cytochrome P-450 2C19.

Note: Subjects requiring amifostine or rituximab must be aware of the increased risk of orthostatic hypotension with the addition of telmisartan. Any subject requiring lithium therapy while on study must have lithium levels monitored closely by their outside physician. All subjects on the above listed medications should provide documentation that this physician is aware of the study protocol.

4.2.4 Subjects with untreated hyperlipidemia must be willing to abstain from initiating therapy for the 24 week duration of the study. Subjects on a stable (>12 weeks) lipid-lowering regimen must be willing to remain on their current dose for the 24 week study duration.

4.2.5 Subjects undergoing treatment for diabetes with oral hypoglycemic agents must be willing to remain on their current dose of insulin-sensitizing agents (metformin/biguanides) for the duration of the study. Titration of other diabetes medications will be permitted.

4.2.6 Screening laboratory values as follows:

- ANC < 750 cells/mm^3

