### **Visit 2 Baseline (Week 0, within 30 days of screening)**

Once eligibility has been confirmed, the subject will be scheduled for baseline evaluation, which includes safety lab evaluation and the collection of stored serum, plasma, and urine samples for future analyses. Telmisartan 40 mg po daily will be distributed at this evaluation, and the subject will be counseled (again) regarding adherence and potential medication side effects.

For all subsequent visits, evaluations should be performed +/- 14 days from the expected date. Medication adherence/compliance and method of birth control (if applicable) will be assessed and documented at every visit.

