### **Visit 8 (Week 24)**

This visit will be the final study visit. A targeted physical exam, safety laboratory evaluation, and the collection of banked serum, plasma, and urine samples will be performed. A single 5 mm slice CT scan at the level of L4-L5 will be scheduled within 14 days of this visit, and the image will be sent to the central reading center in electronic format. After this visit, telmisartan will no longer be provided by the study. However, should a subject wish to continue to take telmisartan, he or she may do so by prescription from their primary care provider.

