### **9.3 Primary Endpoint Assessments**

VAT volume (cm^2) will be calculated from a single 5 mm slice CT scan obtained at the level of the L4-L5 inter-vertebral disc space. CT scans will be obtained prior to telmisartan initiation and at study termination (Weeks 0 and 24). All CT scans will be standardized and communicated via electronic medium (CD, DVD, or optic disk) to the central reading center at Tufts University. The central reader will be blinded to patient characteristics.

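### The 48-hour pregnancy test is tied to entry and not to the first CT, so that scan may rest on a screening test up to about 30 days old

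*Protocol*

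**What the plan says.** The first CT appears in the visit text of protocol section 6.2 only under Visit I Screening: "If eligible, the subject will undergo a single 5 mm slice CT scan at the level of L4-L5". The sentence that governs its timing is "The CT scan will not be scheduled until eligibility is confirmed by exam and laboratory parameters". The next visit is headed "Baseline (Week 0, within 30 days of screening"), and its text does not mention a CT.

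Two other sections place the scan at Baseline. The Schedule of Events (6.1) marks the first CT in the Baseline column and leaves the Screen column blank. Section 9.3 says "CT scans will be obtained prior to telmisartan initiation and at study termination (Weeks 0 and 24").

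On pregnancy testing, 4.2.1 says that women of reproductive potential "will need a negative serum or urine pregnancy test in the 48 hours prior to entry". The safety labs defined under the 6.1 table include the test ("serum creatinine], urine or serum pregnancy test"). Before treatment they are marked at Screen and Baseline only. Section 6.6 adds a test whenever pregnancy is suspected.

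On contraception, 4.2.1 says that, where sexual activity could lead to pregnancy, "study participants must use contraception while on study drug and for 4 weeks after going off study drug". Section 6.3 stops CT scans for subjects who become pregnant after entry.

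**The concern.** Section 6.3 shows that the protocol means to keep CT away from pregnant subjects, and 4.2.1 shows that it wants a recent negative test before a woman enters. The two safeguards are not joined for the first scan. Section 6.2 sets an earliest point for that scan, and the recent test is anchored to a later event.

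A woman could test negative at screening, conceive in the interval, and have a research abdominal CT before the entry test shows the pregnancy. The stated contraception requirement starts with study drug, so it does not cover that interval. Section 6.3 applies after entry, so it does not cover it either.

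What is at stake is participant safety. The primary comparison is not, because a woman excluded at entry never starts telmisartan and is replaced under 6.4.

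**Working it through.** The protocol gives no figure to reproduce here. The check is a count of days.

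**Inputs**

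- Screening, with the first pregnancy test: day 0 (6.1).
- Baseline, which is entry: day G, with 0 ≤ G ≤ 30 (6.2, Visit 2).
- Entry pregnancy test: e days before entry, with 0 ≤ e ≤ 2 (4.2.1, 48 hours).
- First CT: any day from confirmed eligibility to the first dose on day G (6.2, 9.3).
- Scheduled pregnancy tests between screening and the entry test: none (6.1, 6.6).

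The 14-day visit allowance in 6.2 applies only to visits after Baseline, so it does not lengthen G.

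**Case A: CT on the Baseline day, after the entry test.** The latest test is at most 2 days old.

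**Case B: CT before the entry test.** The latest scheduled test is the screening test. Its age is greatest when the CT comes just before the entry test:

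maximum age = G − e, which runs from G − 2 (entry test taken 48 hours ahead) to G (entry test on the Baseline day, after the scan).

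| Gap G, screening to Baseline | Maximum test age at CT, Case B | Maximum test age at CT, Case A |
|---|---|---|
| 7 days | 7 − 2 = 5, to 7 days | 2 days |
| 14 days | 14 − 2 = 12, to 14 days | 2 days |
| 30 days | 30 − 2 = 28, to 30 days | 2 days |

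**Does the text rule out Case B?** Three places might.

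1. *The Baseline mark in 6.1.* The second CT carries the matching mark at Week 24, yet the Visit 8 text says "A single 5 mm slice CT scan at the level of L4-L5 will be scheduled within 14 days of this visit". A mark in the table therefore does not by itself fix the scan to the visit day.
2. *The Week 0 label in 9.3.* The firm requirement there is that the scan precede the drug. A scan some days before Baseline meets it.
3. *The eligibility condition in 6.2.* It could be read to include the 48-hour test. But 6.2 has eligibility confirmed before Baseline is scheduled, the safety labs then follow at Baseline, and 4.2.6 refers to screening laboratory values. The screening test can satisfy the condition.

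Even on the Baseline day, no section says that the pregnancy test comes before the scan.

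**The case against.** The strongest reply is that one reading fits every section. The CT is marked at Baseline in 6.1, in the same column as the safety labs with their pregnancy test, and 9.3 agrees. The 6.2 sentence is a restriction, and reading it as leave to scan on any earlier day stretches it. Where the protocol wants a window around a CT, as at Week 24, it writes one, and it writes none for the first CT. Pregnancy is itself an exclusion with the 48-hour test inside it, so a woman might not count as eligible until that test is negative.

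Much of this stands. A Baseline-day scan satisfies 6.1, 6.2 and 9.3 together, so the sections do not contradict each other, and sites may well scan that way. It does not close the gap. Section 6.2 places the first scan under the screening visit with only a not-before condition, and no section orders the test ahead of the scan.

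Other safeguards also reduce the risk. A screening test always precedes the scan in women of reproductive potential. Testing is repeated on suspicion. Method of birth control is to be assessed and recorded at every visit. The 30-day figure needs Baseline at its limit and a scan just ahead of the entry test; a CT soon after the screening results would rest on a fresher test. The Manual of Operations, to which 6.5 refers for CT instructions, and the consent form are not shown, and either may already deal with this.

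**Conclusion.** The point holds as a minor safety and scheduling gap. As written, the protocol permits the first CT to be done on the strength of a screening pregnancy test that is at worst 28 to 30 days old. With the scan placed after the entry test, the maximum is 2 days.

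This rests on two readings: that entry means Baseline, as the fasting footnote to 6.1 indicates, and that the eligibility condition for the CT can be met by screening results. The actual gaps, the day on which sites would scan and the number of women of reproductive potential among the 35 subjects are not stated. The figures are therefore upper limits, and no rate of exposure can be derived. Confidence is medium, chiefly because the CT instructions cannot be seen.

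**What to change.** Add one sentence to 6.2: the baseline CT is done at the Baseline visit, after the negative entry pregnancy test that 4.2.1 already requires and before the first dose of telmisartan. If sites need to scan earlier, require a negative urine test within 48 hours before the CT in women of reproductive potential.

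The first option adds no test but needs a CT slot on the Baseline day ahead of dosing. The second costs at most one extra urine test per woman of reproductive potential. Neither changes the endpoint, the sample size or the analysis.

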### **Visit 2 Baseline (Week 0, within 30 days of screening)**

Once eligibility has been confirmed, the subject will be scheduled for baseline evaluation, which includes safety lab evaluation and the collection of stored serum, plasma, and urine samples for future analyses. Telmisartan 40 mg po daily will be distributed at this evaluation, and the subject will be counseled (again) regarding adherence and potential medication side effects.

For all subsequent visits, evaluations should be performed +/- 14 days from the expected date. Medication adherence/compliance and method of birth control (if applicable) will be assessed and documented at every visit.

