## **4.0 SELECTION AND ENROLLMENT OF SUBJECTS**

### **4.1 Inclusion Criteria**

- 4.1.1 HIV positive men and women age 18 and older.
- 4.1.2 HIV-1 infection, as documented by any licensed ELISA test kit and confirmed by Western blot at any time prior to study entry or plasma HIV-1 RNA > 2000 on two occasions.
- 4.1.3 Documented central fat accumulation (defined for women/men as: waist circumference > 94/95 cm or a waist-to-hip ratio > 0.88/0.94).
- 4.1.4 HIV-1 RNA documented to be less than 50 copies/mL at screening and undetectable by assay of choice (<50 or <400) for at least 12 weeks prior to entry.
- 4.1.5 Current antiretroviral therapy with a suppressive, highly active anti-retroviral regimen. Subjects must not have changed ART in the 12 weeks prior to entry, and must not be planning to change ART for the 24 week study duration.
- 4.1.6 Systolic blood pressure >115mmHg. Telmisartan has been demonstrated to be safe for use in normotensive subjects.
- 4.1.7 Ability and willingness of subject to provide informed consent.

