### **Visits 3 and 4 (Weeks 1 and 2)**

These visits will assess blood pressure and any subject-reported adverse events 7 and 14 days, respectively, following initiation of telmisartan. No laboratory evaluations will be performed unless prompted by adverse events.

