#### Premature Study Treatment/Background ART Discontinuation Evaluations

Subjects who discontinue telmisartan due to adverse events or by personal choice will be followed and asked to complete the Week 12 and Week 24 evaluations (as listed in the Schedule of Events (section 6.1)) prior to being taken off study.

Subjects who discontinue their background ART entry regimen for  $\geq 14$  consecutive days due to toxicity or adherence will be asked to complete the Week 12 and Week 24 evaluations prior to being taken off study.

Subjects experiencing drops in systolic blood pressure below 100mmHg (without sequelae) or asymptomatic increases in serum creatinine, AST, ALT, or alkaline phosphatase (to  $<3\times$  ULN for liver enzymes) may temporarily discontinue telmisartan. When systolic blood pressure returns to  $>100\text{mmHg}$  and/or if laboratory abnormalities resolve within 14 days, telmisartan may be restarted at the discretion of the study physician and subject at a dose of 20 mg po daily. The subject should be monitored closely for tolerability. If the subject does not experience a recurrence of the adverse event, he/she may continue on telmisartan for the duration of the study.

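### The ±14-day visit window also applies at Weeks 1 and 2, so the first two on-treatment blood-pressure checks can fall on Days 21 and 28 within protocol

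*Protocol*

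**What the plan says.** Under the Visit 2 Baseline heading of section 6.2, the protocol states: "For all subsequent visits, evaluations should be performed +/- 14 days from the expected date". Study drug starts from the same visit: "Telmisartan 40 mg po daily will be distributed at this evaluation".

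The next entry in 6.2, for Visits 3 and 4, gives the purpose and target days of the early visits: "These visits will assess blood pressure and any subject-reported adverse events 7 and 14 days, respectively, following initiation of telmisartan". It plans no laboratory tests at either visit unless an adverse event calls for them. The schedule of events in 6.1 lists a targeted exam with blood pressure at Weeks 1, 2, 6, 12, 18 and 24 and gives no visit-specific windows.

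Two safety rules use the blood-pressure reading. Section 5.1 allows a reduction to 20 mg if a subject's "sbp becomes <100mmHg or serum creatinine significantly increases". Section 6.4 allows temporary interruption, and a restart at 20 mg, when systolic pressure falls below 100 mmHg without sequelae.

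On who may enter, criterion 4.1.6 reads: "Systolic blood pressure >115mmHg. Telmisartan has been demonstrated to be safe for use in normotensive subjects". Under 4.2.2, subjects already on a stable antihypertensive regimen are eligible, but "they must be willing to add telmisartan to their current regimen" and must bring the prescriber's agreement.

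**The concern.** A fixed tolerance of 14 days suits a visit many weeks into treatment. At Weeks 1 and 2 it is as long as, or longer than, the time since the first dose, so it no longer defines an early check.

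What is at stake is early safety monitoring. Describing safety and tolerability is a primary objective (1.2.2). All subjects start at the full 40 mg dose. A subject may enter with a systolic pressure only just above 115 mmHg, about 115 − 100 = 15 mmHg from the level at which the protocol allows the dose to be cut or paused. Others will be adding telmisartan to existing antihypertensives. Low pressure without symptoms is found by measuring it, and before Week 6 these two visits are the only planned measurements on treatment.

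**Working it through.** **Inputs**
- Tolerance: ±14 days for all visits after baseline (6.2, Visit 2 Baseline).
- Target days: Day 7 and Day 14 after the first dose (6.2, Visits 3 and 4); Weeks 6, 12, 18 and 24 taken as Days 42, 84, 126 and 168 (6.1).
- Assumption: the first dose is on Day 0, the day drug is dispensed, with one dose per day. A check on Day *d* is then preceded by about *d* doses.

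**Formulas**
- Earliest day = target − 14; latest day = target + 14.
- Relative tolerance = 14 / target day.

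**Results**

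| Visit | Target day | Earliest | Latest | 14 / target |
|---|---|---|---|---|
| Week 1 | 7 | −7 | 21 | 200% |
| Week 2 | 14 | 0 | 28 | 100% |
| Week 6 | 42 | 28 | 56 | 33% |
| Week 12 | 84 | 70 | 98 | 17% |
| Week 18 | 126 | 112 | 140 | 11% |
| Week 24 | 168 | 154 | 182 | 8% |

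**Reading the table**
- Taken literally, the Week 1 window opens a week before the first dose and the Week 2 window opens on the day of the first dose. Both visits are meant to follow initiation, so only days after the first dose count.
- The Week 1 and Week 2 windows overlap from Day 0 to Day 21. A single date can satisfy either visit.
- The latest Week 2 day (28) is also the earliest Week 6 day (28).
- Doses before the first planned check: 21 at the latest permitted day against 7 on target, a difference of 21 − 7 = 14.

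**Does anything else in the protocol narrow the window?** The other timing tolerances are: baseline within 30 days of screening (6.2), the final CT within 14 days of the Week 24 visit (6.2), and a 7-day return for subjects who arrive not fasting (6.6). None concerns the Week 1 or Week 2 visit.

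**What is not affected.** The visceral fat and blood-pressure endpoints are changes from Week 0 to Week 24 (9.3, 9.4), so the timing of Weeks 1 and 2 does not enter them or the sample size in 9.1. No laboratory tests are planned at Weeks 1 and 2, so the window delays no creatinine result; only the blood-pressure part of the dose-reduction rule is concerned.

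**Width of a workable window.** With targets 7 days apart, symmetric windows of ±*w* do not overlap if 7 + *w* < 14 − *w*, that is *w* < 3.5. The widest whole-day choice is therefore ±3:
- Week 1: 7 ± 3 = Days 4 to 10.
- Week 2: 14 ± 3 = Days 11 to 17, ending 28 − 17 = 11 days before the Week 6 window opens.

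A choice of ±2 gives Days 5 to 9 and 12 to 16.

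**The case against.** The strongest reply is that the text for Visits 3 and 4 is the more specific. It is the only on-treatment visit entry that fixes days after the first dose, and a coordinator could take it to govern. The same text is used above to rule out a Week 1 visit before dosing, so it may seem uneven not to let it limit the late end too. This does not succeed. A visit before the first dose cannot be an on-treatment check at all, whereas a visit on Day 21 still follows initiation. The stated days are the expected dates, and the general rule measures its tolerance from the expected date, for all later visits without exception. The Manual of Operations might set a narrower window, but it is not at hand, and section 6.2 does not refer to it for visit timing.

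Other points do stand, and they limit the weight of the finding:
- Day 21 and Day 28 are upper limits. The targets remain Days 7 and 14, and nothing suggests that a single site with 35 subjects would routinely book late.
- The percentages describe the shape of the rule. They do not measure risk.
- Dose reduction and interruption are not tied to a visit. Subjects are counselled on side effects when drug is dispensed, and a symptomatic problem can be acted on when it is reported.
- The population is restricted: a blood-pressure floor at entry, prescriber agreement for those on antihypertensives, no other angiotensin receptor blockers, no unstable coronary disease or decompensated heart failure.
- A tighter window cannot make a subject attend. It does make a late check visible as a deviation.

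**Conclusion.** The concern holds. As written, the protocol lets the Day 7 and Day 14 blood-pressure checks take place on Days 21 and 28, which defeats the stated purpose of the only scheduled on-treatment safety contacts before Week 6. The size is up to 14 extra daily doses before the first planned measurement, and a second check that can coincide with the opening of the Week 6 window.

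This rests on the general window applying literally to Weeks 1 and 2, on a first dose on the day of dispensing, and on no narrower rule existing elsewhere. It is a permitted delay, not a demonstrated harm: early findings would come later, not be lost. The point should be corrected because correction is cheap and serves a primary safety objective. It does not threaten the efficacy conclusions.

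**What to change.** In section 6.2, limit the ±14-day tolerance to Week 6 and later, and add a separate window for the two early visits. Possible wording: *The Week 1 and Week 2 visits are to be done within 3 days either side of Day 7 and Day 14 after the first dose (Days 4 to 10 and Days 11 to 17); visits from Week 6 onward may be done within 14 days either side of the expected date.* The ±3 days is a proposal and comes from no document. The clinical team should confirm the width.

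The cost is one amended sentence and slightly tighter booking of two visits at a single site. No assessment is added, and neither the sample size nor the analysis changes. At the latest permitted day, about 10 doses would precede the first check instead of 21.
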